## Methodology

### Study design

It is a cluster randomized controlled trial. A formative research will follow a mixed-methods approach to achieve the objectives of the study. Mixed method research that contains both qualitative and quantitative approaches is commonly used to explore the context of an issue and combines the strengths and lessens the weaknesses in both approaches within a single study.

We are proposing a mixed method design in which the qualitative research will precede the quantitative.

| Qualitative component            | Quantitative component                |
|----------------------------------|---------------------------------------|
| 1. Focus group discussion (FGDs) | 3. KAP survey                         |
| 2. In-depth Interviews (IDIs)    | 4. Health facility surveys and audits |
|                                  | 5. Implementation research            |

For the qualitative component focus group discussions (FGDs) and in-depth interviews (IDIs) will be conducted on different target groups.

For the quantitative component a baseline knowledge attitude & practices (KAP) survey will be conducted on 10% of the population. We will also conduct assessments and audits of all the health facilities within the target areas. The findings of IDIs, FGDs and KAP survey would give an insight on the acceptability of proposed package of care. Also based on findings we will devise the best way to implement the proposed EmONC package in community.

### Study Site

The Study will be conducted in Tehsil Rahim Yar Khan of District Rahim Yar Khan (RYK). The District Rahim Yar Khan (population~4,580,000) is one of the largest districts of southern Punjab, consisting of four sub-divisions (Tehsils) i.e. Sadiqabad, Rahim Yar Khan, Khanpur and Liaquatpur.

District Rahim Yar Khan has been selected as the target district not only because of alarming Maternal and Child health indicators but because of the presence and strong community connection of Women and Child Health division of Aga Khan University. The University has a project office at Rahim Yar Khan from where major Flood Relief Activities were done; another major nutrition intervention project was carried out in the district through the involvement of Lady Health workers and local government. Hence these contributions and connections with the LHW program, local government and community provide a feasible environment for the Aga Khan University to undertake this project.

#### GENERAL DEMOGRAPHIC INFORMATION OF DISTRICT RAHIM YAR KHAN

| Indicators                                         |               |
|----------------------------------------------------|---------------|
| Population                                         | 4578538       |
| The land area of the district                      | 11880 sq.km   |
| Average Annual Growth Rate                         | 3.2%          |
| Population density                                 | 385/square KM |
| Infant < 1 yr (expected in 2010)                   | 123621        |
| Children < 5 yr (expected in 2010)                 | 613524        |
| LHWs (expected in 2010)                            | 1851          |
| Women in child bearing age (expected in 2010)      | 1007278       |
| Married child bearing age women (expected in 2010) | 732566        |
| Expected pregnancies (expected in 2010)            | 155670        |

[figure not shown]

The highest number of population is in Rahim Yar Khan Tehsil (1444531) and the lowest number of population is in Khanpur (995728). The rural population is more (82%) than the urban (18%) population. In terms of population demographic, there are more females (52%) compared to males (48%) in the district and almost half majorities? (44%) of people are below 15 years of age.

#### Tehsil wise distribution

| Tehsil | Number Of UC | Population |
|--------|--------------|------------|
|--------|--------------|------------|

|                |    |         |
|----------------|----|---------|
| Khanpur        | 28 | 995728  |
| Liaquatpur     | 25 | 1005625 |
| Rahim Yar Khan | 40 | 1444531 |
| Sadiqabad      | 29 | 1132654 |

|              | DHQ | THQ | RHC | BHU | Dispensaries |
|--------------|-----|-----|-----|-----|--------------|
| District RYK | 01  | 04  | 19  | 104 | 56           |
| Tehsil RYK   |     | 1   | 5   | 30  | 16           |

### Health Indicators

| Indicators               |                         |
|--------------------------|-------------------------|
| Infant Mortality Rate    | 98/1000 live births     |
| Under 5 mortality Rate   | 148/1000 live births    |
| Maternal mortality Ratio | 103/100,000 live births |

Sources: MICS 2007-08 and EDOH Office Rahim Yar Khan

### Research snapshot

[figure not shown]

### Study Approaches

#### Qualitative Component

In order to conduct a comprehensive research in the community and to implement suitable interventions, it is imperative that accurate information on the etiology of maternal and neonatal morbidity and mortality is available. This, however, is difficult as much of the information on mortality/morbidity trends and associated outcomes is only available from hospital-based cohorts. It is therefore, crucial to collate such information from community. Also, in order to

incorporate culturally sensitive and logistically appropriate factors, we need to understand the target population. Therefore, this initial phase of qualitative research will help us in understanding the embedded problems and also an in-depth evaluation of knowledge, attitude and practices of families and primary care providers (TBAs, LHWs, LHV and BHU/RHC staff) will assist us in understanding the health situation in study area. These issues are with regards to

- Common causes of maternal morbidity in pregnancy
- Maternal nutrition and dietary patterns during pregnancy
- Determinants of care seeking behavior during pregnancy and labor
  - Domiciliary versus hospital births
  - Selection of care givers by families
  - Reasons for referral by primary care givers
- Knowledge, Perception and recognition of danger signs during pregnancy and child birth by families and care givers
- Immediate and early newborn care practices (colostrum and prelacteal feeding, breastfeeding, cord care, temperature regulation, swaddling, skin care etc.)
- Concepts of early neonatal morbidity and health seeking behavior e.g.
  - Risk factors for birth asphyxia
  - Low birth weight and temperature regulation)
  - Neonatal infection (local and generalized)
  - Seizures or spasms
  - Respiratory problems

## 1. Sampling Methodology:

We are proposing purposive sampling according to the framework in following tables to ensure to include population from poor and marginalized groups received representation. Sample size for qualitative research usually depends on the resources, time available, and a study's objectives. Purposive sample sizes are often drawn on the extent of level of data saturation. It is the point in data collection when new data no longer bring additional insights to the research questions or objectives. Purposive sampling is most successful when data review and analysis are done in conjunction with data collection. The sample size for FGDs and IDIs are as follows:

### Sample size for Focus Group Discussions& IDIs (Tehsil Rahim Yar Khan):

| Respondents                             | Research Methods | No. of Interviews / Discussions |
|-----------------------------------------|------------------|---------------------------------|
| Recently Delivered Women                | IDIs             | 06                              |
| Currently Pregnant Women                | IDIs             | 06                              |
| Lady Health Workers                     | FGDs             | 02                              |
| Traditional Birth Attendants            | FGDs             | 02                              |
| Community Midwives                      | IDIs             | 06                              |
| Community Leaders                       | IDIs             | 04                              |
| Male decision makers in HH              | FGDs             | 02                              |
| Female decision makers in HH            | FGDs             | 02                              |
| Executive District Officer (Health)     | IDIs             | 01                              |
| District Coordinator (National Program) | IDIs             | 01                              |
| CMW Coordinator                         | IDIs             | 01                              |

|                    |      |    |
|--------------------|------|----|
| General Physicians | IDIs | 02 |
| Pediatricians      | IDIs | 02 |
| Gynecologists      | IDIs | 02 |

## 2. Sample Size Calculation for KAP Survey (Tehsil RYK):

We will also conduct a KAP survey during the initial baseline survey which will be done in the target study area. We will implement the cluster sampling methodology for KAP survey. For the calculation of sample for the KAP survey we have selected the household as a Primary Sampling Unit (PSU) for our survey and we will select one women of reproductive age from each household. Firstly we will calculate the sample size required for the survey and then this sample size will be distributed through cluster sampling in target union councils (household will be selected systematically i.e. every  $k^{\text{th}}$  from random starting point). The overall calculation for the sample size is as follows. Using the formula for calculating sample size:

$$N = Z^2 (p) (q) / d^2 \times DE$$

Assuming

- $Z=1.96$ . (Confidence interval)
- $p$  and  $q=(1-p) = 0.5$  by assuming a 50/50 split in responses across questions. (Refers to the proportion of the population with the attribute we are looking).
- $d = 5\%$  refers to the desired precision of the estimate.
- $DE = 2$  (Design effect)

$$N = (1.96)^2 (.5)(.5) / 0.05^2 \times 2 = 768$$

### Quantitative approach:

**Cluster randomized control trial** will be used to evaluate the impact of EmONC package for maternal and neonatal health care delivery through community level health care providers. Clusters will be identified and matched on population size, socio-economic status (including structure, electricity, drinking water with HH density), birth/death rates, and number of functional LHWs and CMWs. Cluster Paired randomization will be done to allocate one group (intervention/control) to each cluster and all the LHWs in one union council will be assigned to one group to avoid any sort of contamination.

**Sample Size Calculation:** We are considering Union Council as a cluster. Each Union council serves approximately 15000 - 20000 population and usually contains a Basic health Unit which provides basic facilities of antenatal, natal and post natal care.

- We assume that the average cluster size is 15000 and considering a crude annual birth rate of 20 per 1000 and the estimated average perinatal mortality rate of 60/1000 with a coefficient of variation between clusters of 0.125 and to detect a 25% reduction in the mortality rates, we would require **20 Clusters** in total. Ten clusters per arm to provide the study with a power of 90% over a three-year intervention period.

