## **2. Statistical analysis of Quantitative Data**

For data analysis SPSS version 19 will be used and data will be analyzed using univariate and multivariate methods. Reports will be generated fortnightly for senior management of project to review the progress of implementation of interventions.

Primary analysis will be undertaken as intention-to-treat at cluster level. All usual residents of a household who have resided in the study area for >15 days in succession during the 6 months prior to delivery, and delivered during the study period will be considered eligible for analysis, regardless of the place of delivery. Analysis will be done at cluster level using SPSS 19.0 (SPSS Inc., Chicago, Illinois, USA). To account for clustering, point estimates for SBRs, NMRs and perinatal mortality rates for each study arm will be calculated as the mean of cluster event rates, giving an equal weight to each cluster. We will undertake both unadjusted and adjusted analysis of outcomes. We will similarly evaluate differences between intervention and control clusters for cause specific NMR although the study is only powered for the primary all cause neonatal mortality outcomes. Ideally, randomization will take care of confounders, but based on the analysis of baseline characteristics, we will adjust other confounders (if any).

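### Clusters are randomised in matched pairs, but the pairing is carried into neither the sample size nor the stated primary analysis

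*Protocol*

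**What the plan says.** In the protocol section on the quantitative approach, union councils are the clusters. "Clusters will be identified and matched on population size, socio-economic status", and also on birth and death rates and on numbers of functional community health workers and midwives. Allocation follows the matching: "Cluster Paired randomization will be done to allocate one group (intervention/control) to each cluster". Twenty clusters in total imply 10 pairs, although the number of pairs is not written down.

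The sample size paragraph in the same section assumes that "the average cluster size is 15000 and considering a crude annual birth rate of 20 per 1000", takes "the estimated average perinatal mortality rate of 60/1000" with a "coefficient of variation between clusters of 0.125", and aims "to detect a 25% reduction in the mortality rates". It concludes: "Ten clusters per arm to provide the study with a power of 90% over a three-year intervention period". It gives no within-pair CV, no matching correlation, no alpha and no sidedness.

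The section on statistical analysis of quantitative data sets an intention-to-treat analysis at cluster level, in which "point estimates for SBRs, NMRs and perinatal mortality rates for each study arm will be calculated as the mean of cluster event rates", each cluster weighted equally. Unadjusted and adjusted analyses are planned. The pairs do not appear, and no test or variance formula is named.

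**The concern.** Matching and paired randomisation are a design choice that pays off only through the analysis. If paired clusters have similar underlying mortality, the difference within a pair is less variable than the difference between two unrelated clusters. An analysis by arm treats that shared part as noise.

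Two things are at stake. First, the power claim: the variance that drives a paired comparison is the variance within pairs, and a paired test on 10 pairs has 9 degrees of freedom rather than 18. A figure built on between-cluster variation and clusters per arm does not describe that comparison. Second, the test and interval: if the pairs are alike and are ignored, the standard error is too large and the test rejects less often than its nominal level, so the gain for which the matching was done is lost.

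**Working it through.** **Inputs, all from the sample size paragraph.** Births per cluster: 15,000 × 20/1000 × 3 years = 900. Control rate p0 = 0.060; intervention rate p1 = 0.75 × 0.060 = 0.045; difference 0.015. CV k = 0.125. Ten clusters per arm. Alpha is not stated; two-sided 5% is assumed.

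**Formula** (Hayes–Bennett, c clusters per arm or c pairs):

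c = a + (z_α + z_β)² × V/(p0 − p1)², with V = p0(1 − p0)/n + p1(1 − p1)/n + k²(p0² + p1²); a = 1 unmatched, a = 2 pair-matched, where k is then the within-pair CV.

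V = 0.0564/900 + 0.042975/900 + 0.015625 × 0.005625 = 0.0000627 + 0.0000478 + 0.0000879 = 0.0001983. V/0.015² = 0.0001983/0.000225 = 0.8814.

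**Reproducing the protocol's figure (unmatched).** For 90% power, (1.960 + 1.282)² = 10.507, and 10.507 × 0.8814 = 9.26, so c = 10.26. Power at c = 10 is Φ(√(9/0.8814) − 1.96) = Φ(1.236) = 89.2% (89.0% by noncentral t with 18 df). This matches the stated 90% within about one point.

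**Same inputs, 10 pairs analysed as pairs, matching removes no variance.** c = 2 + 9.26 = 11.26, so 12 pairs for 90%. Power at 10 pairs is Φ(√(8/0.8814) − 1.96) = Φ(1.053) = 85.4% (84.9% by noncentral t with 9 df; 85.2% by simulation).

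**How much matching restores 90%.** With within-pair CV 0.104: V = 0.0001104 + 0.010816 × 0.005625 = 0.0001713; V/0.000225 = 0.761; Φ(√(8/0.761) − 1.96) = 90.0%. By the same formula, power is 88.8% at 0.11 and 90.8% at 0.10. Taking within-pair variance as k²(1 − ρ), a CV of 0.104 corresponds to a pair correlation of true rates ρ = 1 − (0.104/0.125)² ≈ 0.31.

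**Effect of ignoring the pairs.** Under no effect, the variance of one cluster rate is 0.0564/900 + 0.015625 × 0.0036 = 0.0000627 + 0.0000563 = 0.0001189, of which a share 0.0000563/0.0001189 = 0.473 is between-cluster. The observed pair correlation is therefore 0.473ρ, and the unpaired standard error is too large by a factor 1/√(1 − 0.473ρ): 1.08 at ρ = 0.3 and 1.22 at ρ = 0.7. No document gives ρ; 0.3 to 0.7 is an assumed range. Simulated type I error of the unpaired test (18 df) is about 3.7%, 2.8% and 2.0% at ρ = 0.3, 0.5 and 0.7. The paired test stays near 5%.

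Simulation of both analyses, 100,000 trials per row (power and mean 95% half-width under the 25% reduction):

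| ρ | Type I, unpaired | Power, unpaired | Power, paired | Half-width per 1000, unpaired | Half-width per 1000, paired |
|---|---|---|---|---|---|
| 0 | 4.9% | 89.2% | 85.2% | 9.2 | 9.8 |
| 0.25 | 3.9% | 90.3% | 88.9% | 9.2 | 9.3 |
| 0.5 | 2.8% | 91.4% | 92.4% | 9.2 | 8.7 |
| 0.75 | 1.9% | 92.8% | 95.4% | 9.2 | 8.1 |

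**Point estimate.** With equal weights and complete pairs, the difference between arm means of cluster rates equals the mean of the 10 within-pair differences, so pairing does not change the estimated rate difference.

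**The case against.** The strongest reply is that the protocol names no test and no variance formula. Its equal-weight arm means are compatible with a paired analysis, and a statistical analysis plan that is not shown may specify one. That stands in part: the absence of a test is not itself a fault, and the document nowhere commits to an unpaired test. What remains is that the protocol does fix a power figure, a level of analysis, an estimator and weights, all by arm, next to an allocation by pair.

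A reader might infer that true power is 85% and also that the intervals will be too wide. The two do not hold together. The 85% assumes that matching removes no variance, and then the unpaired interval is the narrower one and keeps its level. Intervals are too wide only if matching works, and then 10 pairs do better than 85%. If the analysis were unpaired, power would be about 89% to 93%, close to the stated figure.

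A reader might also infer that ten per arm can only come from the unmatched formula. It cannot be settled: one-sided 5% with the matched formula gives 9.55, hence 10 pairs (91.4% power). The unmatched two-sided reading is likelier, because the CV is labelled as between clusters, the count is per arm, and the one critical value the protocol shows (1.96, for the KAP survey) is two-sided.

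Finally, the power shortfall depends on 900 births per cluster. The protocol's own district tables suggest more: 1,444,531/40 people × 123,621/4,578,538 infants × 3 years ≈ 2,925. Then V/0.000225 = 0.542, and 10 pairs have Φ(√(8/0.542) − 1.96) ≈ 97% power even with no gain from matching. In that case only the question of the standard error and test remains.

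**Conclusion.** The point holds as a moderate one. The design is pair-matched, while the sample size and the stated primary analysis are written as for two unmatched arms. At the protocol's inputs and an assumed two-sided 5%, the 90% is most naturally the unmatched 89%. For 10 pairs analysed as pairs, power is about 85% with no gain from matching and reaches 90% at a within-pair CV of about 0.104 or lower.

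Ignoring effective matching (pair correlation 0.3 to 0.7, an assumption) would make the test conservative, at about 3.7% to 2.0% instead of 5%. Ineffective matching would leave the unpaired test at its level. There is no bias and no excess of false positives, so the trial's validity is not threatened. What is lost is efficiency and a power statement that fits the design.

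**What to change.** In the section on statistical analysis of quantitative data, make the primary comparison the within-pair difference in cluster rates, or in log rates, over the 10 randomised pairs, with 9 degrees of freedom. If log rates are chosen, the estimator wording must change as well, because the result is then a ratio of geometric means rather than a comparison of arithmetic arm means.

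In the sample size paragraph, state alpha and sidedness, say whether 0.125 is the CV between clusters or within pairs, and restate power for 10 pairs as about 85% (no matching gain) to about 90% (within-pair CV about 0.104).

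Settle this before any outcomes are compared by arm. The dissemination section plans an interim comparison after one year of intervention, and choosing between paired and unpaired analysis after that would be open to the results.

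The cost is wording only, with no added clusters or data. The statistical price is 9 fewer degrees of freedom: if matching proves useless, power is about 85% rather than 89%.

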### EmONC Package:

On the basis global and local literature available around the maternal and neonatal care and survival, a comprehensive EmONC package is developed to be rolled out in the target areas of District RYK.

**Operational definition of Emergency Obstetric and Newborn Care**

**Basic EmOC:**

- Parenteral antibiotics
- Parenteral oxytocics
- Parenteral anti-convulsants and anti-hypertensives
- Manual removal of placenta
- Removal of retained products (MVA)
- Assisted vaginal delivery (forceps, vacuum extraction)

**Comprehensive EmOC:**

- All 6 basic functions plus:
- Blood transfusion
- Cesarean section

**Emergency Obstetric and Newborn Care (EmONC)** (in addition to the above)

- Neonatal resuscitation;
- Hypothermia Management (re-warming);
- Antibiotics for neonatal sepsis (injectable and oral);
- Essential newborn care.

***Demand side interventions***

**a) *Community Mobilization/Community Supports Groups:***

To create awareness in the community and at the household level in intervention clusters, information for empowerment and change (IEC) strategy for women and their husbands through female and male supports groups will be formed/ strengthened. The LHWs will identify and train community facilitators. Female activist will form female support groups and male activists will form male support groups in the LHW catchment area. These activists will enter and raise awareness about MNH and will work with community to identify and invite those most likely to be affected such as poor and marginalized.

These facilitators will be trained on disseminating awareness on antenatal care, identification of danger signs related to pregnancy and recognition for high-risk pregnancies and births (these include maternal malnutrition, illness, short stature, previous perinatal deaths etc.), birth preparedness (skilled birth attendant, facility), essential & immediate newborn care and recognition of danger signs and management low birth weight and sepsis with early and appropriate referral. An emergency fund will be established in community support groups for active referral and transportation of the complicated cases for the provision of EmONC. These community groups will aid in establishing funds from the local resources and families will be asked to contribute whatever is in their capacity, and utilization of these funds will be monitored by the person from community in charge for this activity so that each family benefit equally.

The LHWs and the family members in the intervention community will also be sent informational/educational messages on their mobile phones to highlight the importance of maternal and newborn health. The contact numbers will be collected during the base line survey.

